## Study processes

We aim to recruit patients registered with general practices in Greater Manchester, which participated in a renal collaborative project established by the Collaboration for Leadership in Applied Health Research and Care (CLAHRC) for Greater Manchester [55]. A number of these practices will be in areas of socioeconomic disadvantage as identified by Index of Multiple Deprivation (IMD) scores.

## Patient recruitment and randomisation

Practices will be offered options for how to recruit patients from their CKD disease register to the study. These options will include:

1. Telephone contact will be made by a member of the practice team to patients due to be seen for a vascular disease review and/or if the GP or nurse prefer, through raising the study at the end of the consultation. These patients will be informed about the BRIGHT trial and asked if their contact details can be forwarded to the BRIGHT team for them to be contacted for further information.
2. Patients due to be seen for a disease review will be sent an invitation and information sheet by their general practice and asked to return a form agreeing to be contacted (see Figure 2).

Patients who agree to participate in the trial will be sent Part 1 of the baseline questionnaire to be completed prior to a meeting with a researcher. A researcher will then arrange to meet with the patient at a time and place convenient for them. Once consented, the researcher will collect Part 1 of the questionnaire and then complete Part 2 of the baseline questionnaire with the patient. The baseline questionnaire is divided in this way to reduce the burden on participants at one time point. In addition, some measures in Part 2 of the baseline questionnaire are optimally delivered at a face-to-face interview because of their relative complexity.

Following completion of the questionnaires, the clinical trials unit will be contacted (by phone or online) and the patient will be allocated to a trial arm via a minimization algorithm (incorporating a random component) to maximize balance between the two arms on key prognostic factors. Minimization will be performed with respect to age, smoking status and evidence of other vascular disease, and will be stratified by practice. Allocation is centralized to prevent the researcher from consciously or unconsciously affecting the patient selection process. This approach will prevent selection bias and will maximize the precision of the treatment effect estimates by ensuring balance between arms with respect to practice recruitment rates and the minimization factors.

[figure not shown]

This approach will prevent selection bias and will maximize the precision of the estimates of the treatment effects by ensuring balance between arms on the selected key variables. Although observer bias does not apply in this case, researchers are blinded to prevent any chance of them consciously or unconsciously affecting the patient selection process.

The patient will be informed of their allocation to either control or intervention group immediately after the baseline interview. If allocated to the intervention the patient will be given a kidney information guidebook, website information and the PLANS booklet. They will be informed that they will receive a phone call from a peer support worker in one week to discuss the PLANS options in the booklet/website. Practices will be informed of patient participation in the trial.

### Sample size calculation

The study is designed to have 80% power to detect a standardized effect size of 0.25 on the primary outcome of self-management between the control and intervention arms. This is a relatively small effect, but is in line with most sizes of effect observed in our previous trials of self-management interventions. Using an alpha of 0.05, and assuming a correlation of 0.5 between outcome measures at baseline and follow-up (a conservative estimate), and 25% attrition of participants, we will recruit 500 patients across both arms of the trial. We aim to recruit 16 to 18 practices and to recruit 28 to 32 patients from each practice.

### Analysis

For each of the outcomes, multilevel regression analysis will be used to examine differences between trial arms.

For binary outcomes (for example, BP control) the model will be logistic regression; for continuous outcomes the model will be linear regression. All analyses will follow intention-to-treat principles and a pre-specified analysis plan. Primary analyses will control for baseline scores and the design factors (practice, age-group, smoking status, and additional vascular disease). Where appropriate, sensitivity analyses will be conducted (for example, treating all missing BP data as failures; control for additional covariates; bootstrapped *P* values for skewed outcomes). All analysis will be undertaken using Stata version 12 (<http://www.stata.com>) and an alpha level of 5%. In the case of missing data values, we will apply mean imputation and regression imputation where rates are low, and consider multiple imputation where they exceed 10%.

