**Methods/Designs**

**Design overview**

The study is a two-arm, patient-randomized, RCT. Participants will be primary care patients registered with general practices with an existing diagnosis of stage 3 CKD. Participants will be allocated to one of two groups: an intervention group or a control group. The intervention group will receive the BRIGHT intervention, to be delivered after a recent clinical appointment with a GP or practice nurse. Participants in the control group will receive care as usual from their general practice and will be provided with the guidebook and website link at the end of the trial. Patient data will be collected at two time points: at baseline (prior to group allocation and intervention delivery) and at six months post-intervention. The reporting of this trial follows the Consolidated Standards of Reporting Trials (CONSORT) guidelines [41-43].

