## Outcomes

All outcomes are at the level of the patient. The primary end-point will be the six-month follow-up for patient health outcomes and costs. The trial has three primary outcomes: one clinical outcome of blood pressure control (dichotomized as controlled versus not controlled) and two patient-reported outcomes of 1) self-management ability, and 2) health-related quality of life (see Additional file 1). Secondary outcomes include additional measures of self-management ability, health status, anxiety (general and CKD-specific), loneliness, medication adherence, social networks and social involvement. Information on service utilization and resource use will also be collected for use in a cost-effectiveness analysis (see below). Each patient will complete a baseline questionnaire, and a follow-up questionnaire will be sent at six months (see Additional file 1).

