### **Missing data**

The cost-effectiveness analysis will apply imputation techniques to address the statistical issues related to the presence of missing resource use and health outcome data. Imputation of missing data will be conducted using STATA software and will use recommended techniques such as multiple imputation.

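### The protocol commits to mean and regression imputation of missing values at low rates without excluding outcomes, where it understates standard errors or dilutes the effect

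*Protocol*

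**What the plan says.** The Analysis section plans multilevel linear regression for continuous outcomes and logistic regression for binary ones. The primary analyses adjust for baseline score, practice and the minimisation factors, at a 5% alpha. For missing values, "we will apply mean imputation and regression imputation where rates are low, and consider multiple imputation where they exceed 10" per cent. The section does not define a low rate; 10% is the only figure it gives. It does not say whether the rule covers outcomes, covariates or single items, and it does not exempt binary outcomes. Counting missing blood pressure as failure appears only as an example of a sensitivity analysis.

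The Outcomes section names three primary outcomes: self-management ability, health-related quality of life and dichotomised blood pressure control.

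The Sample size calculation aims for "80% power to detect a standardized effect size of 0.25 on the primary outcome of self-management". Its assumptions are stated as "Using an alpha of 0.05, and assuming a correlation of 0.5 between outcome measures at baseline and follow-up" and "25% attrition of participants, we will recruit 500 patients across both arms of the trial".

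For the economic evaluation, the separate Missing data section states that imputation "will use recommended techniques such as multiple imputation".

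**The concern.** Single imputation replaces an unknown outcome with one fixed number. A mean or a fitted regression value has no scatter around it, so each filled-in patient lowers the residual variance and also adds to the apparent sample size. What follows depends on whether the imputation uses arm:

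- **With arm** (arm-specific mean, or regression including arm), the effect estimate is unbiased but its standard error is too small.
- **Without arm** (overall mean, or regression on baseline only), the filled-in patients show no treatment difference, so the estimate moves towards zero.

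The protocol does not say which applies, so the direction of the error is unknown too. For blood pressure control, the mean of a 0/1 variable is a proportion, which is not a valid value for a logistic regression outcome. At stake are the intervals and p-values, or the effect size, of primary outcomes analysed under this rule.

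**Working it through.** **Inputs from the protocol.** N = 500, effect d = 0.25 SD, baseline–follow-up correlation r = 0.5, alpha 0.05, power 80%, attrition 25%. **Assumed, because not stated:** two-sided alpha and 1:1 allocation. **Simplifications:** values missing completely at random, no clustering by practice.

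**1. Reproduce the sample size.** With baseline adjustment the outcome variance is 1 − 0.5² = 0.75.

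n per arm = 2 × (1.960 + 0.842)² × 0.75 / 0.25² ≈ 189, or 378 in total.

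For attrition: 378 / 0.75 = 504, in line with the planned 500. Without baseline adjustment the result would be 672, so the plan used the adjusted variance. The design therefore counts on information from about 500 × 0.75 = 375 patients, for which the formula gives 79.8% power.

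**2. Standard error when imputation uses arm.** Let m be the share missing.

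- True SE, carried by the observed patients: √[4 × 0.75 / (500(1 − m))].
- SE the model reports: the residual variance falls to 0.75(1 − m) while N stays at 500, giving √[4 × 0.75(1 − m) / 500].
- Ratio, reported to true: 1 − m.

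At m = 0.10 this is 0.0735 against 0.0816, a ratio of 0.90. The actual type I error is 2Φ(−1.96(1 − m)):

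- m = 0.05: 2Φ(−1.862) ≈ 6.3%
- m = 0.10: 2Φ(−1.764) ≈ 7.8%

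**3. Effect when imputation ignores arm.** The expected estimate is d(1 − m): 0.25 × 0.95 ≈ 0.24 and 0.25 × 0.90 ≈ 0.23.

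**4. Simulation check** (6,000 trials per scenario; baseline-adjusted linear model):

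| Handling of missing outcomes | Type I error, 5% missing | Type I error, 10% missing | Estimate of 0.25, 5% missing | Estimate of 0.25, 10% missing |
|---|---|---|---|---|
| Arm-specific mean | 6.4% | 8.0% | 0.249 | 0.251 |
| Regression with arm | 6.4% | 7.7% | 0.249 | 0.251 |
| Overall mean | 5.1% | 5.1% | 0.236 | 0.226 |
| Regression without arm | 5.2% | 4.9% | 0.237 | 0.225 |
| Observed outcomes only | 5.2% | 4.9% | 0.249 | 0.251 |

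**5. Blood pressure control.** The section on registered prevalence of CKD reports between 51% and 91% of patients at target across practices. Over that range a mean-imputed value lies between 0.51 and 0.91, neither 0 nor 1. If it were rounded, every missing patient would become controlled, the reverse of the plan's failure-based sensitivity analysis. An assumed 10-point difference between arms would then become 10 × 0.90 = 9 points at 10% missing.

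**6. The alternative at 25% missing.** Observed outcomes: type I error 4.9%, power 78%. Multiple imputation with arm and baseline in the model (20 imputations, 2,000 trials): type I error 4.7%, power 79%. Both match what the sample size was built to deliver.

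**The case against.** Four objections have weight.

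- **The rule may not be meant for outcomes.** Missing values could mean stray items or covariates, where simple imputation at low rates is acceptable. The sample size is inflated for attrition, which presupposes that dropouts are not filled back in. This reading is possible, but the text does not state it, and the sentence stands in the outcome-analysis section shortly after missing blood pressure is discussed.
- **An analysis plan may settle it.** The protocol refers to a pre-specified plan that is not shown. Details such as a definition of low, or a firmer commitment above 10%, may properly sit there. The protocol nevertheless names a method, and that method is unsuitable for outcomes.
- **The worst figures lie outside the rule.** A reader might combine the single-imputation sentence with "25% attrition of participants" and infer a type I error of about 14%, or an effect diluted to about 0.19. Those would arise only if single imputation were used at 25% missing. The text does not prescribe that; it points towards multiple imputation there.
- **Regression imputation is not ruled out for binary data.** It can draw or classify a 0/1 value, and the protocol does not say that its regression imputation omits a random residual, although that is the usual meaning of the term. The point about fractions is strict only for mean imputation.

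A reader might also infer that EQ-5D would be completed in two conflicting ways, since the economic section favours multiple imputation. The documents do not support this: the details of the primary quality-of-life measure are in Additional file 1, which is not shown, and the economic sentence concerns that analysis only.

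**Conclusion.** The concern holds for low missing rates. Followed as written for outcomes with up to 10% missing, the rule either raises type I error from 5% to about 6.3% (5% missing) and about 8% (10% missing), or shrinks an effect of 0.25 to about 0.24 and 0.23. Mean imputation does not produce a usable value for blood pressure control. Above 10%, where the plan expects to be, the protocol prescribes no damaging method, but it commits to none either.

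The figures rest on values missing completely at random, 1:1 allocation, a two-sided test and no clustering. The harm is moderate and easily avoided: this should be fixed, but it does not threaten the design.

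**What to change.** Replace the imputation sentence with three statements:

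1. Mean or regression imputation is limited to missing baseline covariates, and to questionnaire items where the instrument's scoring rules allow it.
2. At any missing rate, the primary analysis of each outcome is the planned multilevel model on observed six-month outcomes, adjusted for baseline score and the design factors.
3. Multiple imputation is a committed sensitivity analysis, with arm, baseline score, design factors and practice in the imputation model, and a logistic model for blood pressure control. It may instead be made the primary analysis, provided the choice is fixed in advance.

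The sample size, data collection and conduct do not change. The cost is slightly more analysis work, and intervals wider than single imputation with arm would report. The sample size has already allowed for the lost information.

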### **Cost-effectiveness analysis**

This evaluation will assess the cost-effectiveness of self-management support compared with usual care.

### **Utilization and resource use**

Resource use data from primary and secondary care contacts will be collected using patient questionnaire at six month follow-up. Questionnaires previously used in large multicentre RCTs will be adapted to capture resource use.

### **Unit costs**

Unit cost estimates from published data sources will be applied to relevant resource use data collected above (for example, cost of GP visit applied to the number of GP visits) to generate a total cost per patient (post-randomization).

### **Intervention costs**

We will estimate the cost of developing and producing the booklet and will also assess the time spent training individuals in telephone support.

### **Measurement of effectiveness within the trial**

For the trial-based economic evaluation, the measure of effect will be the EQ5D [56]. EQ5D will be collected at baseline and then at six months. This instrument can be used to generate Quality Adjusted Life Years (QALYs). The QALY will be calculated using the Area under the Curve method and adjusting for baseline scores on the EQ5D. In addition, regression analyses will be conducted to identify other factors that may affect individual health state; these may include age, gender and the patient's primary diagnosis.

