**Population**

Patients must have a clinical diagnosis of stage 3 CKD and will be identified from disease registers at GP practices. Patients must be able to communicate in English and there will be agreement with practices that the patient is appropriate to be recruited to the trial. Patients receiving palliative care or who have reduced capacity to consent will be excluded from the trial.

Inclusion criteria will be stage 3 chronic kidney disease (both stages 3a and 3b).

Exclusion criteria will be: mental incapacity to provide informed consent; inability to communicate in English; receiving palliative care. Only one person per household will be eligible for the study to avoid potential contamination between control and intervention patients.

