### **Synthesis of costs and outcomes**

If appropriate, cost and QALY data will be synthesized to generate an Incremental Cost-Effectiveness Ratio (ICER) where additional cost of the intervention is formally compared with additional benefits. The ICER can be used to inform the adoption decision. However, economic evaluation is conducted under conditions of uncertainty, which in this data will be represented using cost-effectiveness acceptability curves (CEACs) generated through the use of probabilistic sensitivity analysis. CEACs will plot the probability of self-management support being cost-effective for a range of threshold values of an additional QALY, and will be presented for both the within-trial analysis and (if feasible), the longer term model.

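### The QALY model is fixed only for baseline EQ5D and leaves other covariates to a regression search, without committing to all the factors the trial allocates by

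*Protocol*

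**What the plan says.** Four sections of the protocol bear on this.

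- **Patient recruitment and randomisation** sets the allocation factors: "Minimization will be performed with respect to age, smoking status and evidence of other vascular disease, and will be stratified by practice".
- **Analysis** opens with "For each of the outcomes, multilevel regression analysis will be used to examine differences between trial arms" and then carries the allocation factors into the model: "Primary analyses will control for baseline scores and the design factors (practice, age-group, smoking status, and additional vascular disease". The QALY is not named there.
- **Measurement of effectiveness within the trial** has its own rule. First, "The QALY will be calculated using the Area under the Curve method and adjusting for baseline scores on the EQ5D". Then, as something added to this adjustment: "regression analyses will be conducted to identify other factors that may affect individual health state; these may include age, gender". Primary diagnosis is the third example given.
- **Synthesis of costs and outcomes** expresses uncertainty through "cost-effectiveness acceptability curves (CEACs) generated through the use of probabilistic sensitivity analysis". It does not say which QALY model, or which covariates, feed those curves.

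No section applies the covariate set of the Analysis section to the QALY or to costs.

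**The concern.** The trial balances the arms on four factors, and the protocol justifies this by the precision it brings. The clinical analysis follows through by putting all four in the model. The economic analysis commits to none of them: age appears only as a possible covariate, and practice, smoking status and other vascular disease are not mentioned.

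Two things follow if the text is carried out as written.

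1. A model that omits factors on which allocation was balanced counts their variance as noise, although balancing has largely removed that variance from the difference between arms. The reported standard error then exceeds the true one.
2. Covariates found by regressing the outcome on candidate variables are chosen with the outcome in view. If they enter the QALY model, the adjusted difference depends on which ones are kept.

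The incremental QALY is the denominator of the ICER, which the protocol says can inform the adoption decision. Its model should therefore be settled before the data are seen.

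**Working it through.** **Setting.** The stated sample size reproduces, so its assumptions were used to set up the check. With a standardized effect of 0.25, correlation 0.5, alpha 0.05 (taken as two-sided) and 80% power, the number per arm is 2 × (1.960 + 0.842)² × (1 − 0.5²) / 0.25² = 188.4, rounded up to 189. The total is 378, and 378 / 0.75 = 504, against the stated 500.

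**From EQ5D to QALY.** EQ5D is measured at baseline (E0) and six months (E6) only. The area under the curve is therefore 0.5 years × (E0 + E6)/2 = 0.25 × (E0 + E6). In a linear model that contains E0, the arm coefficient for the QALY is one quarter of the arm coefficient for E6, and so is its standard error. Ratios of standard errors are the same on either scale.

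**Formula.** Let R² be the share of the variance left after baseline EQ5D that the omitted allocation factors explain. If allocation balances them, then

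reported SE / true SE ≈ 1/sqrt(1 − R²).

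The documents give no R², so a range of 0.02 to 0.20 is assumed. If age were kept in the model, only the share due to the other factors would count.

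| Assumed R² | SE ratio | Excess | Actual coverage of a nominal 95% interval | True probability of 0.80 would read |
|---|---|---|---|---|
| 0.02 | 1.010 | 1.0% | 95.2% | 0.798 |
| 0.05 | 1.026 | 2.6% | 95.6% | 0.794 |
| 0.10 | 1.054 | 5.4% | 96.1% | 0.788 |
| 0.20 | 1.118 | 11.8% | 97.2% | 0.774 |

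Coverage is 2Φ(1.96 × ratio) − 1. The last column is Φ(0.842 / ratio). It treats the QALY as the only source of uncertainty, so it illustrates scale and does not predict the trial's acceptability curve, which also depends on costs.

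**Simulation.** Trials of 500 patients in 17 practices were simulated, with minimization containing a random component, 25% attrition unrelated to arm or covariates, a correlation of 0.5 and no treatment effect. There were 1,500 runs per value of R². The results are in standard deviation units.

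| R² | Baseline-only model: mean SE | Baseline-only model: empirical SD | Type I error, baseline only | Type I error, allocation factors added |
|---|---|---|---|---|
| 0.02 | 0.0895 | 0.0874 | 4.8% | 4.5% |
| 0.05 | 0.0895 | 0.0898 | 4.9% | 5.5% |
| 0.10 | 0.0894 | 0.0861 | 3.9% | 5.0% |
| 0.20 | 0.0894 | 0.0816 | 3.6% | 5.3% |

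Monte Carlo error in the rejection rates is about 0.6 percentage points. Bias was at most 0.004 SD with either model. At R² of 0.05 or less, no problem is detectable. At 0.20 the reported standard error is 0.0894 / 0.0816 = 1.096 times the true one, close to the formula.

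**Data-driven selection.** No size can be put on this. The protocol gives neither the candidate list nor the selection rule, and does not say what is done with the factors found.

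**The case against.** A fair defence has four parts.

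- **The list is open and includes age.** This stands. Age is an allocation factor and is named as a possible covariate, and the other three are uncommitted, not excluded. A reader might infer that the QALY analysis will ignore the allocation factors; the text does not go that far.
- **The regressions may be a separate study of what determines health state.** The text never says that the factors found enter the QALY difference, the ICER or the curve, so this reading is possible. The sentence does follow the baseline adjustment directly and is presented as an addition to it, so entry into the model is the more natural reading. The wording should settle the matter either way.
- **Covariates belong in the analysis plan.** The Analysis section refers to a pre-specified plan that is not shown, and that plan may fix the QALY model. An unlisted covariate would be no finding. Here, however, the protocol states a method, namely finding factors by regression, which differs from the fixed set it gives for the primary analyses. A plan that fixes the set would need this sentence brought into line.
- **Any error is conservative and may be negligible.** This stands. In addition, the synthesis section plans no significance test on the QALY, so the type I error figures only indicate calibration.

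**Conclusion.** The point holds as a matter of consistency and pre-specification. The QALY model is committed only to baseline EQ5D, is otherwise left to a search, and does not name three of the four factors by which patients are allocated. If those factors are left out, the QALY difference stays unbiased and its standard error is about 1% to 12% too large for an assumed residual R² of 0.02 to 0.20. This rests on allocation achieving balance, on attrition unrelated to arm or to the factors, and on an R² that the documents do not give. The concern about choice after seeing the data applies only if the identified factors enter the QALY model.

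Three stronger readings are tempting but not supported:

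- **That the QALY intervals and acceptability curve are wrong.** The intervals may be somewhat too wide. The model behind the curve is not stated, and cost uncertainty also shapes it.
- **That precision worth a share of the patients is lost.** Squaring the ratio at R² = 0.20 suggests 1 − 1/1.118² = 20% of the sample. But balanced allocation keeps most of the precision in the estimate itself: its empirical SD at that value was 0.0816 without the factors and 0.0796 with them. The excess lies mainly in the reported standard error.
- **That primary diagnosis cannot vary because everyone has stage 3 CKD.** The term is undefined, both 3a and 3b are admitted, and the Background notes frequent coexisting conditions.

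It is also not established that EQ5D would be analysed under two different models. That would require EQ5D to be the primary quality-of-life measure, and the outcome measures are detailed in an additional file that is not shown.

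This is an improvement that costs nothing, not a demonstrated error.

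**What to change.** Under Measurement of effectiveness within the trial, state the incremental QALY model in advance: QALY on arm, baseline EQ5D, practice, age group, smoking status and other vascular disease, with practice handled as in the Analysis section. Say that this model supplies the QALY difference for the ICER and the within-trial acceptability curve. If any allocation factor is to be left out, give the reason.

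Keep any regression search for predictors of health state, including gender and primary diagnosis, as a labelled exploratory analysis that does not feed the ICER.

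The cost is a change of wording. The allocation factors are recorded at randomization and EQ5D is already collected at baseline, so no new data, visits or patients are needed.
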